#### Pilot Evaluation: Changes Made From Pilot to RCT

In a pilot study in 2012, we tested an intervention based on MI and medication review aimed at improving patients’ beliefs about medicines and adherence to secondary prevention of cardiovascular disease [41]. The pilot RCT of 21 patients resulted in insights regarding the feasibility of the intervention and study design. Patients with more negative beliefs (BMQ-S) changed toward more positive beliefs, but there was no difference between groups at follow-up. A need to stratify the randomization based on baseline beliefs was identified [41]. We tested a method of categorizing patients according to their beliefs in the pilot study population and found that half of the population (10 patients) had an attitude with a potentially negative impact on adherence [42].

In line with the recommendation from the Medical Research Council (MRC) [3], we have also made a qualitative evaluation of the pilot study (not published). Interviews of 8 patients showed that, overall, the patients were positive about the intervention and felt more informed by it. The interviews also informed us that some patients changed their views on medicines in a positive direction, although it was not enough to categorize them to an attitude group with higher adherence. The care processes for these 8 patients were also compared with the theoretical framework of the intervention, and we found that all the patients were affected by some part of the intervention; patients with a negative attitude toward their medicines were mainly affected in the adherence dimensions, whereas patients with a positive attitude were helped in the area of quality of treatment. However, our evaluation showed that not all the dimensions of adherence were well covered in the identification phase of the intervention and that the pharmacist felt the need for more training in MI.

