#### Study Design of the RCT in Brief

The MIMeRiC trial is an RCT with 2 parallel groups (N=418) and 12 months follow-up. Patients with CHD identified and followed at the cardiology clinic of Kalmar County Hospital are randomized to usual care (control) or usual care plus a follow-up program with medication review and MI. Ethical approval has been obtained from the Regional Ethics Committee, Linköping (Dnr-2013/236-31). The trial (clinicaltrials.gov, NCT02102503) has been fully described in the forthcoming protocol [6]. Patients in the intervention group meet a clinical pharmacist at the cardiology clinic 2 to 5 times during the year after discharge depending on need, and problems with adherence or prescribing are solved in collaboration with the patient and/or the cardiologist.

The primary outcome of the trial is the proportion of patients reaching the treatment goal for low-density lipoprotein cholesterol. Secondary outcomes involve the effects on blood pressure, patient adherence, quality of life, and health care use. An economic evaluation of the intervention is also planned.

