### Methods for Research Question 3: Was the MI Used Consistently With MI Principles?

This will be a quantitative assessment of the integrity of MI delivered by the clinical pharmacists. All in-person consultations in the intervention group are audio-recorded if permitted by the patient. A random sample of these recordings, the number corresponding to 20% of in-person consultations, will be coded with the Motivational Interviewing Treatment Integrity behavioral coding system version 4.2.1 (MITI 4.2.1) [44] by an independent coding institute (the MIQA group at the Karolinska Institute, Stockholm). A randomly selected 20 min of these recordings will be coded; for one-third of the consultations, the first 20 min will be coded; for one-third, the middle 20 min will be coded; and for one-third, the last 20 min will be coded. Competency in MI will be described by four global scores: cultivating change talk, softening sustain talk, partnership, and empathy. In addition, the ratios of change talk to sustain talk and questions to reflections will be assessed. These scores and ratios will be related to recommended levels of MI competency. The target behavior of the MI consultations is defined as: start taking medicines regularly or maintain this behavior. Changing a patient’s attitude toward their medicines in a positive direction is a strategy for maintaining or reaching the target behavior of regularly taking the medicines. On the basis of our theoretical framework and our pilot evaluation, we assumed that patients with a negative attitude need the MI component of the intervention, and should have this, whereas accepting patients are considered adherent and the need for MI might be less obvious. These patients are targeted by the intervention partly to maintain their target behavior but primarily to solve other DRPs and to improve the quality of prescribing. However, there is no distinct line between these groups; problems with adherence can arise in the group with an accepting attitude as well. To ensure that both groups are equally represented in the assessment of consultations, we will stratify the samples so that 20% of consultations with patients with a negative attitude and 20% of consultations with patients with an accepting attitude are coded. For the latter group, it might be that DRPs make the target behavior undesirable for a particular drug and, if so, only two of the global scores—partnership and empathy—will be used. Such consultations without a target behavior will be valued on a scale for person-centeredness instead of MI competency. The analysis will inform about the frequency of consultations with a target behavior (among the random sample), the fidelity of MI, and the fidelity of person-centered consultations.

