### Methods for Research Question 5: Did the Intervention Change the Patients’ Beliefs About Their Cardiovascular Medicines?

This will be studied primarily quantitatively, but certain aspects will also be illustrated qualitatively by the interviews with patients.

Data on beliefs about medicines will be collected in the MIMeRiC trial with the BMQ-S instrument administered 3 times: baseline (after the standard care follow-up), after 10 months (during the intervention), and after 15 months (after the intervention). In this study, we will ask the patients to consider only their heart medicines as they answer the BMQ-S. The instrument consists of two subscales, one for the perceived necessity for the drugs and one for perceived concerns about the drugs. The two subscales have 5 items each and are assessed by a 5-point verbal descriptor scale ranging from strongly disagree to strongly agree.

As instructed by the originators, numerals (1-5) will then be assigned to each statement of agreement to summarize each subscale with 5 to 25 points. The difference between the necessity and concern scales (range: −20 to 20) will then be related to the cost-benefit analysis for each patient’s medications. A positive difference means that the patient perceives the benefit of taking the drugs to outweigh the risks of taking the drugs, and the more positive the difference is, the more adherent the patient is supposed to be [9]. It has also been found that categorization based on high (>15) or low (<15) scores on each scale, yielding 4 categories (accepting, ambivalent, neutral, and skeptical) predicts adherence behavior [46,47]. Because the scales have ordered verbal categories, it is not correct to assign numerals and sum them to a global score, because the data are only ordered within the structure while the distance between the agreement statements or the magnitude of them is not known [48]. Even though the categorization also depends on the global sum of each scale, this is a more correct way of handling the data. Therefore, we chose this as our primary outcome in analyzing the effects of the intervention on beliefs. The stratified randomization of patients in the MIMeRiC trial was also based on these four categories.

In this study, we will:

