### Methods for Research Question 7: Did the Intervention Change the Quality of Prescribing?

This will be studied using quantitative methods. There are several models for assessing the appropriateness of prescribing or medication use which have been used in intervention studies of medication reviews [49,50]. For this study with a selected group of patients with CHD, we chose to use a tool developed for this diagnosis: the Medication Assessment Tool for evaluation of secondary prevention of CHD (MAT-CHDsp) [51]. The tool is a summary of review criteria based on clinical guidelines and has been developed for use in clinical audits. Compared with the variables in the Swedish Quality Register SWEDEHEART, in which the proportion of patients with a prescription from a certain drug class is registered, MAT-CHDsp has a more individual application where prescriptions that do not follow the guidelines can be justified if the reason is stated in the EHR. The tool was updated in 2014 based on the European guidelines from 2011 and 2012 for myocardial infarction or acute coronary syndrome and the Swedish guidelines for heart disease from 2011 and was then validated in 22 patients in this study. MAT-CHDsp comprises 28 review criteria for which the assessor chooses *not applicable*, *yes*, *no*, *no information found*, or *no, but this is justified*. As an example, the treatment of a patient with CHD and no left ventricular (LV) dysfunction but with side effects from several statins documented in the EHR would be marked as *not applicable* for the criterion “Patient with CHD with LV dysfunction...is prescribed a beta-blocker” and *no, but justified* for the criterion “Patient with CHD is prescribed atorvastatin or simvastatin.”

The MAT-CHDsp will be applied to a random sample of 20% of the patients in each of the intervention and control group. Data on the prescribing 6 months after discharge will be collected retrospectively from the EHR at assessment. Applicable criteria will then be analyzed for adherence to guidelines or justified nonadherence. The results will be compared between the groups in terms of adherence and justified nonadherence, as a measure of the quality of the prescribing for secondary prevention [52].

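### The prescribing-quality audit (Research Question 7) draws its 20% sample within arm only, so the belief balance from stratified randomisation is not kept; the contrast stays unbiased but loses some precision that could be recovered without extra chart reviews.

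*Protocol article*

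**What the plan says.** Three parts of the protocol article bear on this.

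- **Sampling and comparison for Research Question 7.** "The MAT-CHDsp will be applied to a random sample of 20% of the patients in each of the intervention and control group". Prescribing at 6 months after discharge is read retrospectively from the health record, and "The results will be compared between the groups in terms of adherence and justified nonadherence". No stratum other than arm is named.
- **Randomisation.** Under Pilot Evaluation: "A need to stratify the randomization based on baseline beliefs was identified". Under Research Question 5: "The stratified randomization of patients in the MIMeRiC trial was also based on these four categories", that is, accepting, ambivalent, neutral and skeptical.
- **Where the prescribing benefit is expected.** Under Research Question 3, patients with an accepting attitude are included partly to maintain their behaviour but "primarily to solve other DRPs and to improve the quality of prescribing". The qualitative evaluation of the pilot (8 interviewed patients) found the negative-attitude patients affected mainly in the adherence dimensions, "whereas patients with a positive attitude were helped in the area of quality of treatment".

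**The concern.** By the article's own account, attitude at baseline predicts who should gain in prescribing quality. That attitude is recorded for every patient, because randomisation used it. The audit then takes one patient in five from each arm without using it, so the two audited samples can differ by chance in their share of accepting patients although the full arms were balanced on it.

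Research Question 7 is the only process question that compares the arms on what the medication review is meant to change. Research Question 1 is descriptive and rests on the pharmacists' documentation. The integrated process results are to be used to explain the trial's outcomes, so avoidable noise in this one contrast weakens that explanation.

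**Working it through.** The article gives no sample size, power or variance for Research Question 7, so there is no stated figure to reproduce.

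**Inputs from the article.** Total size and design: "The MIMeRiC trial is an RCT with 2 parallel groups (N=418) and 12 months follow-up". Sampling fraction: 20% within each arm.

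**Assumptions.** Allocation 1:1, since the article says only that patients "are randomized to usual care (control) or usual care plus a follow-up program with medication review and MI". Half of patients accepting; the pilot found half of its patients (10) with a potentially negative attitude. Full arms exactly balanced on attitude. For the precision check: a patient-level score from 0 to 100, residual SD 13, and a 10-point intervention effect in accepting patients only.

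**1. Audited sample.** 418/2 = 209 per arm; 0.20 × 209 = 41.8, about 42 per arm. At an assumed 1:2 allocation it would be about 28 and 56.

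**2. Chance imbalance in the accepting share.** For draws of 42 from 209 in each of two balanced arms:

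SD = √[2 × p(1−p)/42 × (209−42)/208]

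- p = 0.5: √[2 × 0.25/42 × 167/208] = 0.098, 95% range about ±19 points.
- p = 0.2: SD 0.078, 95% range about ±15 points.

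With 42 per arm, a gap of at least 10 points means at least 5 patients. The exact hypergeometric probability at p = 0.5 is 0.27; for at least 15 points (7 patients) it is 0.11. A normal approximation gives 0.31 for the 10-point gap.

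**3. What this does to the contrast.** If attitude shifted the score by 10 or 20 points in both arms, the 95% range of the chance shift in the contrast would be 10 × 0.192 = 1.9 or 20 × 0.192 = 3.8 points.

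**4. Precision recovered.** Let g be the score gap, accepting minus other, under usual care; in the intervention arm the gap is g + 10.

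- Crude variance = 2 × 169/42 + 0.25 × [g² + (g+10)²] × (167/208)/42
- Variance with a proportional stratified draw = 2 × 169/42 = 8.05
- Variance with post-stratification = 8.21, slightly larger because the category counts in the sample vary

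| Assumed g (points) | Crude variance (SE) | Post-stratified / crude | Stratified draw / crude |
|---|---|---|---|
| −20 | 10.44 (3.23) | 0.79 | 0.77 |
| −10 | 8.53 (2.92) | 0.96 | 0.94 |
| −5 | 8.29 (2.88) | 0.99 | 0.97 |
| 0 | 8.53 (2.92) | 0.96 | 0.94 |
| +10 | 10.44 (3.23) | 0.79 | 0.77 |
| +20 | 14.26 (3.78) | 0.58 | 0.56 |

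At g = +10 the SE falls from 3.23 to 2.87, which equals about 53 rather than 42 patients per arm. No case tried showed a loss.

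**5. Where most of the imprecision comes from.** The difference detectable with 80% power at two-sided 0.05 is (1.96 + 0.84) × √(2/n) SD units: 0.61 SD at n = 42 against 0.27 SD at n = 209. The 20% fraction itself accounts for most of the lost precision, and stratifying wins back only part.

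**The case against.** The strongest reply is that nothing here is invalid. A random draw within randomised arms gives an unbiased contrast, and a valid confidence interval already covers chance imbalance. That stands, and it limits the point to efficiency.

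Several further objections also stand, against stronger readings that a reader might infer:

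- **That stratified randomisation was meant to protect the prescribing contrast.** The stated reason is balance of baseline beliefs, from a pilot about beliefs and adherence. The link to prescribing is indirect, through the expectation that accepting patients gain mainly there.
- **That Research Question 7 contradicts Research Question 3.** The latter stratifies its 20% of consultations so that both attitude groups are represented in a fidelity assessment within the intervention arm. It is not a device for balancing arms, so there is no inconsistency.
- **That the covariates of Research Question 5 are wrongly left out.** The article calls sex, age, type and history of CHD influential for beliefs, not for prescribing scores. Naming no covariates is silence, and an analysis plan not shown may supply them.
- **That case mix is uncontrolled.** The audit tool scores only applicable criteria and accepts documented justification, which deals with part of the clinical mix.

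The size of the gain is also open. The article suggests that the effect differs by attitude; it does not say that prescribing under usual care does. With a gap of 0 to −10 points almost nothing is gained.

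One objection does not fully succeed: that the draw is mere detail left to another document. The article states the sampling rule and names arm as its only stratum. It says random rather than simple random, so a stratified draw is not excluded, but none is stated.

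**Conclusion.** The point holds as a minor design point. As stated, the audit does not secure the belief balance that randomisation gave the full trial, although the article expects the prescribing effect to depend on belief category. With about 42 patients per arm and half of them accepting, the accepting share differs between arms with an SD of about 10 points.

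The consequence is some lost precision, not bias. Using the category lowers the variance by about 1% to 42% with post-stratification, and slightly more with a stratified draw. That range rests on assumed 1:1 allocation, 50% accepting, residual SD 13, a 10-point effect in accepting patients only, and score gaps of −20 to +20 points, none of which the article gives. A reader should not infer that the planned comparison is confounded, or that stratifying would make up for auditing only one patient in five.

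**What to change.** Draw the Research Question 7 sample as 20% within each arm by baseline BMQ-S category, merging to accepting versus other if cells are small. If the sample is already drawn, post-stratify to each arm's full category totals, or adjust the comparison for the category. Report the between-arm difference with its confidence interval, so that a wide interval is not read as unchanged prescribing.

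Adjustment for sex, age, type and history of CHD, and separate contrasts for accepting and other patients, are optional; about 84 audited patients will not support much of either.

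The cost is a changed random draw or one line of analysis, plus one sentence in the protocol. No extra patients or chart reviews are needed.

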### Integrating Results of Analysis

Some process evaluation questions will be analyzed before and others will be analyzed after the outcomes of the MIMeRiC RCT are known. This will be determined by time and availability of the data as we prioritize having the results of the RCT ready as soon as all data can be analyzed.

The 7 research questions for the process evaluation will be analyzed by their respective methods and then, when all are complete, the analysis will be combined and applied to the results of the MIMeRiC trial. This will help us understand whether any effects of the intervention are related to the concepts we used in the design. If appropriate, we may carry out additional analyses to test hypotheses generated from integration of the process evaluation data with the trial outcomes; an example of this would be an analysis of the effect of BMQ-S on adherence. The full report of the process evaluation will be published in a peer-reviewed journal and a summary of the findings of and cross-references to the main MIMeRiC trial will aid interpretation of the evaluation.

## Results

Collection of data has been ongoing as part of the MIMeRiC trial, and some process evaluation analyses can start during 2017. The MITI-coding of 64 consultations have been conducted, but the results are not yet analyzed. The method of focus groups and deductive content analysis have been piloted and found to be useful for the question about how patients experience the intervention, and more focus group interviews will be conducted in September 2017.

## Discussion

This paper describes the framework for the design of the intervention tested in the MIMeRiC trial, development of the intervention from the pilot stage to the complete trial intervention, and the framework and methods for the process evaluation. Providing the protocol of the process evaluation allows prespecification of the processes that will be evaluated, because we hypothesize that they will determine the outcomes of the MIMeRiC trial. This protocol also constitutes a contribution to the new field of process evaluations as made explicit in health services research and clinical trials of complex interventions. The two active parts of the intervention, motivational interviewing and medication review, are both quantitatively evaluated with their specific instruments: Motivational Interviewing Treatment Integrity (MITI) coding and categorization of all DRPs acted on, as well as assessment of secondary prevention treatment quality. Qualitative methods are used to inform about patients’ experiences of the intervention and to capture any unforeseen effects on the secondary care process experienced by patients.

A limitation might be that we are a small research team and have been the designers, implementers, as well as evaluators of this complex intervention. This may not be in line with the guidelines of the MRC. However, the guidelines for process evaluation of complex interventions issued by the MRC in 2015 have served us well in defining the requirements for properly evaluating our intervention process. We hope that this protocol can inspire other research teams to publish process evaluation protocols so that complex interventions in health services research in general, and medication adherence in particular, can be interpreted with more confidence in the future.

## Appendix

Multimedia Appendix 1 Conceptual model of change processes in the intervention. The variables we aim to affect are shown in orange, the goal of optimal treatment is shown in yellow, outcomes measured in the randomized controlled trial are shown in green, and the blue lines represent how the two accompanying parts of the intervention act on the variables. The adherence variable is determined by factors identified by the reasoned action approach (The prescribing variable is determined by adherence to guidelines and the level of individualization.). The consequences of inappropriate prescribing are shown in gray boxes; these interact with factors that influence adherence. CHD: coronary heart disease; EBM: evidence-based medicine.

Multimedia Appendix 2 Conceptual model of intervention change processes and what will be covered by the process evaluation. This figure shows more detail of how we expect the motivational interviewing and medication review to act on determinants of adherence and prescribing. More attention, a nonspecific part of any extra follow-up intervention, shown as a blue oval, is thought to act positively on patients' attitudes toward and subjective norms about adherence. Blue arrows indicate what will be assessed by the intervention and red arrows indicate what determinants we think can be influenced by it. The gray boxes contain the research questions for the process evaluation. CHD: coronary heart disease; EBM: evidence-based medicine.

